### Participant timeline

A schematic schedule of enrolment, interventions and assessments is shown in Fig. 1.

**Fig. 1 Fig1:**
[figure not shown]
EACH-B schedule of enrolment, interventions and assessments. Superscript digit one indicates each time point represents a period of 1 month from baseline testing

### Sample size

Unpublished analysis of earlier data from LifeLab indicates an intra-school (class) correlation coefficient of 0.035. Forty-six schools each sending two classes amounting to approximately 50 students from each school and 2300 students in total will provide 90% power at a 0.025% significance level (accounting for two primary outcomes) to detect a 0.25 SD difference in diet quality score or minutes of total PA in intervention and control schools. Comparable effect sizes have been considered in other health interventions as meaningful in terms of change in health behaviours, and our level of 0.25 SDs falls in the mid-range of effect sizes reported in a meta-synthesis of meta-analyses of behaviour change interventions in the general population [57]. We will recruit two Year 8 classes (12–13 years) from 50 schools allowing for drop-out, though in previous LifeLab studies only one school has ever dropped out. To minimise bias from loss of students to follow-up, we will request class lists for each participating class, so that missing participants at each stage of the follow-up can be identified and included in secondary analyses and process evaluation assessing uptake of the intervention.

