### Trial design

EACH-B is a cluster randomised controlled trial using a 1:1 allocation within a superiority framework. The intervention consists of three-components: (1) face-to-face support from teachers trained in skills to support behaviour change, (2) engagement in the LifeLab school-based education programme and (3) a digital intervention with games as well as peer- and parent-support features.

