#### Primary outcomes

The trial has co-primary outcomes for dietary quality and PA. Dietary quality will be assessed by a 20-item food frequency questionnaire (FFQ). This FFQ has been developed specifically for use with adolescents using data for boys and girls aged 11–18 years who took part in the National Diet and Nutrition Survey. Principal component analysis was applied to these data in order to identify 20 indicator foods which best describe better and poorer dietary quality of UK adolescents. This FFQ has shown good comparison with important nutritional biomarkers including 25-hydroxy vitamin D, total carotenoids, serum folate and vitamin C. Using GENEActiv™ accelerometers PA will be assessed as minutes of daily low, moderate and vigorous physical activity (LMVPA), also described as total PA [48]. At baseline and again at the 12-month follow-up, GENEActivs will be worn for 7 days and the output data will be averaged over this period, or the maximum period of valid data.

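### The significance level is printed as 0.025%, but the sample size gives the stated 90% power at 2.5%; at the printed level power would be about 38–49%

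*Protocol article*

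**What the plan says.** The Primary outcomes section states: "The trial has co-primary outcomes for dietary quality and PA". The Sample size section gives the remaining ingredients. Earlier LifeLab data "indicates an intra-school (class) correlation coefficient of 0.035". The design is "Forty-six schools each sending two classes amounting to approximately 50 students from each school and 2300 students in total", and this number "will provide 90% power at a 0.025% significance level (accounting for two primary outcomes) to detect a 0.25 SD difference". The difference applies to either outcome, diet quality score or minutes of total physical activity. The Trial design section gives 1:1 allocation and a superiority framework. Fifty schools are to be recruited to allow for drop-out from the 46 required.

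The article does not say whether the tests are one- or two-sided and does not state an overall 5% level. The Statistical methods section names no significance level.

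**The concern.** The parenthesis in the power statement explains the reduced level as an allowance for two primary outcomes. Sharing 5% equally between two tests gives 0.05 / 2 = 0.025, or 2.5%. The text prints 0.025%, which is 0.00025. It appears that a proportion was given a percent sign.

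Two things follow if the figure is taken as written. First, the power statement contradicts itself, because the number of schools, the correlation and the effect size do not give 90% power at that level. Second, the only significance level published for the co-primary outcomes is not the one the design supports. If it were carried into the analysis, a primary outcome with p = 0.01 would be declared negative at 0.025% and positive at 2.5%. Readers should not have to infer which level was pre-specified, and a correction made after the results are known would invite the charge that the level was chosen to suit them.

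**Working it through.** **Inputs**

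- Schools: 46, so 23 per arm under 1:1 allocation (Sample size; Trial design).
- Students per school: 50, so 2300 in total (Sample size).
- Intra-school correlation: 0.035 (Sample size).
- Difference to detect: 0.25 SD (Sample size).
- Significance level: 0.00025 as printed; 0.025 as the alternative.
- Assumed, because not stated: two-sided tests, and clustering at school level (the unit randomised).

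**Common steps**

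1. Design effect = 1 + (50 − 1) × 0.035 = 2.715.
2. Effective sample size = 2300 / 2.715 = 847.1, or 423.6 per arm.
3. Standard error of the difference = √(4 / 847.1) = 0.0687 SD.
4. Standardised effect = 0.25 / 0.0687 = 3.638 (unrounded standard error).

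**Reproducing the stated 90%, with 2.5% two-sided**

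- Normal approximation: critical value 2.241; power = Φ(3.638 − 2.241) = Φ(1.397) = 91.9%.
- Noncentral t with 46 − 2 = 44 df: 90.2%.
- With 44 schools the t-based power is 88.7%, so 46 is the smallest even number of schools that reaches 90% by that method.

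**At the printed 0.025%, two-sided**

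- Normal approximation: critical value 3.662; power = Φ(3.638 − 3.662) = Φ(−0.024) = 49.0%.
- Noncentral t, 44 df: 38.3%.

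**Smallest difference that would be significant (normal approximation)**

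- At 2.5%: 2.241 × 0.0687 = 0.154 SD.
- At 0.025%: 3.662 × 0.0687 = 0.252 SD, just above the 0.25 SD target.

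**Schools needed for 90% power (normal approximation)**

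Per arm before clustering, n = 2 × (critical value + 1.282)² / 0.25².

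- At 2.5%: n = 398. Total = 2 × 398 × 2.715 = 2161 students, or 43.2 schools, so 44 in equal arms.
- At 0.025%: n = 783. Total = 2 × 783 × 2.715 = 4252 students, or 85.0 schools, so 86 in equal arms.

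**Can another reading rescue the printed level?**

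| Reading | Power at 0.025% (t to normal) |
|---|---|
| 46 schools, two-sided | 38.3% to 49.0% |
| 46 schools, one-sided | 46.4% to 56.3% |
| All 50 schools, two-sided | 44.8% to 55.2% |
| 92 classes of 25, two-sided | 72.3% to 77.6% |
| 92 classes of 25, one-sided | 78.5% to 82.6% |

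None reaches 90%. The class-level reading was tried because the article's label for the correlation is ambiguous between school and class. It also fails at 2.5% two-sided, where it gives 98.3% to 98.5%, well above the stated 90%.

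**The case against.** The strongest reply is that this is a stray percent sign and not a design fault. The sentence itself mentions the two primary outcomes, so an informed reader can recover 0.025, and the number of schools, the number of students and the power all agree with that reading. On the evident level the trial has about 90–92% power, and nothing in its conduct has to change. This stands. The low power figures describe the printed level, not the design the authors meant.

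A second reply is that the Sample size section gives a planning input and not a testing rule, and that a statistical analysis plan, not shown here, may fix the threshold. This stands in part: the p = 0.01 example is conditional on the printed level being used for testing. But the figure is stated and wrong in the article, and nothing else in the article corrects it.

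A third reply is that 2.5%, two-sidedness and the overall 5% are inferences. That is correct. A one-sided 2.5% test gives 94.5% to 95.3%, so two-sided 2.5% fits the stated 90% better, but the authors must confirm it. The 38–49% range likewise rests on two-sided tests and school-level clustering. It also leaves out the planned baseline adjustment: with an assumed baseline to follow-up correlation of 0.5 (the article gives none), power at 0.025% would be about 59–70%. The article does not say that this adjustment entered the sample size, and the result is still well short of 90%.

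**Conclusion.** The concern holds. The printed 0.025% is inconsistent with the power stated in the same sentence. With two-sided tests and school-level clusters, the stated inputs give 90.2% to 91.9% power at 2.5% and 38.3% to 49.0% at 0.025%, a shortfall of more than 40 percentage points against the stated 90%. No reading tried that allows for clustering brings the printed level to 90%; the most favourable, one-sided with class-level clusters, gives 78.5% to 82.6%. The sample size itself is sound at 2.5%. What is wrong is the only significance level the article states for its two primary outcomes, and the trial's conclusions depend on that figure.

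**What to change.** In the Sample size section, replace the printed level with a 2.5% two-sided significance level for each primary outcome, 5% overall, after the authors confirm that two-sided tests and an overall 5% were intended. Check that the full protocol and any statistical analysis plan carry the same level, and apply it to both primary analyses. Make the correction, dated, before outcome data are compared between arms.

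The cost is one corrected figure in the protocol and the article. The number of schools, the number of students, the effect size and the analysis model stay as they are.

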### Recruitment

Recruitment for EACH-B began in September 2019 and will run for 2 years, with data collection taking place at schools at baseline and again 12 months later. The LifeLab team has worked with schools for many years and good systems for recruiting schools have been developed, so recruitment difficulties are not anticipated. We appreciate that control schools will not want to miss out on the intervention and therefore all control schools will be offered a visit to LifeLab the following year. The schedule of enrolment for the trial is shown in Fig. 1.

Schools will be recruited through a range of methods including presentations at relevant local meetings such as the Secondary Heads of Science forum meetings, and letters sent to Head Teachers and Heads of Science of eligible schools in the recruitment catchment area. The recruitment pack for EACH-B includes a cover letter and information sheet for the school, offering basic information about the trial and explaining how the experience will differ for control and intervention schools. Schools are then offered a meeting with the EACH-B research team at which further details are discussed and any questions answered. This meeting will take place with the Head of Science and a member of the Senior Leadership Team at the school, at a time to suit them. It is also an opportunity for the research team and the school staff to establish how the intervention will run in the school, if it is allocated to the intervention arm, as each school operates differently in terms of timetabling science classes.

Schools will be asked to allocate two middle ability Year 8 classes to participate in the trial totalling approximately 50 students. The teaching programme is designed for students in this age group and of all ability levels; there are no exclusion criteria for students. For students who may require more input (those who have English as a second language, for example), we provide support for schools in planning delivery of the module. Specifics are discussed at the teachers’ PD day. Schools will already have in place provision for these students, and so it is a matter of ensuring that the LifeLab materials are accessible by all participating students.

Following the meeting at school, the Head Teacher is asked to sign a consent form confirming they wish to take part, that they understand the trial procedures and to name the two classes that will participate.

### Randomisation/blinding

After signed agreement from the schools has been obtained and the classes taking part have been identified, schools will be randomised to receive usual schooling (control) or the EACH-B intervention (LifeLab programme, HCS training for teachers, and access to the digital intervention) (see Fig. 1). We will use a minimisation procedure developed by the Southampton Clinical Trials Unit (TENALEA), which aims to achieve a balance of schools in the two arms based on the following three criteria:
The proportion of students in the school receiving free school meals (cut-off > 24%);The proportion of students in the school achieving L5 GCSE (equivalent to a high ‘C’ grade) in English and Maths (cut-off > 40%);Whether or not the school already participated in the full LifeLab programme in the previous 2 years.

The randomisation is administered through a web-based secure system to which the EACH-B team submit the details of schools who have consented to participate. These are sequentially numbered and the allocation to intervention or control is then reported to the investigators. Blinding from this point onwards is not possible except of the statisticians who will be analysing the data.

Many schools we recruit will have previously been involved in LifeLab. Contamination of the intervention effect is unlikely to occur as the Year 8 students taking part in EACH-B will not have visited LifeLab before, and except for siblings, they will generally have limited contact with older children in the school. It will not be possible to blind schools and their students to their allocation due to the nature of the intervention.

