#### Professional development for teachers

The EACH-B intervention includes professional development (PD) for all teachers involved in delivering the LifeLab educational module. The 1-day PD training course takes place at LifeLab and focuses on science education relevant to the implementation of the nine lessons in school. It offers access to online support materials which describe the underpinning science. Teachers are trained in HCS [37, 38] to engage with their students in making plans to improve their diet and/or activity levels via a personal ‘LifeLab pledge’. Teachers are trained how to support their students to keep their pledges, and how to use the digital intervention, through asking open questions and listening rather than telling. An additional HCS training session will be offered to the whole staff body in intervention schools to enhance the opportunity for adolescents to be supported at school to improve their health behaviour.

HCS training was developed in Southampton to provide communication skills to support behaviour change. These skills were designed in the first instance for health and social care practitioners to use with their patients and clients, but have since been adapted to the training of teachers to enable them to better support behaviour change in their students. While health promotion is not seen as a core requirement of a teacher’s role, we have seen high levels of engagement from teachers throughout the development work and EACH-B pilot trial. It is widely acknowledged both in the scientific literature and by schools that diet and PA behaviours are significant factors in both academic performance and student wellbeing and there is growing evidence that health and health behaviours have measurable consequences for attainment [39]. Being more physically active at age 11 is associated with higher attainment at GCSE, while being obese at age 11 is associated with lower attainment [40, 41]. Children from more disadvantaged backgrounds are more likely to be overweight/obese, have poorer diets and be less physically active. Being overweight/obese can reduce children’s self-esteem, which may lead to lower educational attainment and behavioural problems [39]. Therefore, schools and teachers are keen to learn skills that enable them to support students to eat well and be more active.

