#### Statistical methods

Data will be analysed using Stata, SPSS and Mplus. The primary analyses will be according to the intention-to-treat principle, comparing dietary quality and PA levels in the intervention and control groups using mixed effects linear regression to account for clustering within schools. The main analysis will compare these outcomes at baseline and at 12 months follow-up. Although randomised at the level of schools using a minimisation algorithm, there may still be disparities between the intervention and control participants at baseline. These will be assessed prior to analysis and relevant confounders will be incorporated in the models; factors to be considered include gender, exact age at recruitment and household area of deprivation using the Income of Deprivation Affecting Children Index (IDACI) score [58]. Adjustment for baseline dietary quality and PA levels will be included in the relevant models to allow an assessment of change from baseline. Sensitivity analyses will examine effects of missing data, and multiple imputation will be used where appropriate, accounting for the clustered nature of the data.

Comparisons for secondary outcomes will also be modelled using mixed effects linear regression, with the use of binary models for binary outcome variables. Mixed effect logistic regression will be used for rare outcomes and mixed effect binary regression (or Poisson regression with robust variance if the binary regression models fail to converge) will be used for outcomes that occur in more than 10% of students. We will then conduct a mediation analysis to examine the role of these secondary factors in mediating the effect of the intervention on primary outcomes. The main analyses will be conducted using the latest available version of Stata.

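### The three minimisation factors are not named as covariates in the primary models, and the rule of adjusting after a look at baseline disparities would tend not to select them

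*Protocol article*

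**What the plan says.** The Randomisation/blinding section describes a minimisation procedure "which aims to achieve a balance of schools in the two arms based on the following three criteria". The criteria are all at school level:
- the share of students receiving free school meals (cut-off 24%);
- the share reaching the L5 GCSE standard in English and Maths (cut-off 40%);
- whether the school took part in the full LifeLab programme in the previous two years.

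The Statistical methods section sets the primary model as an intention-to-treat comparison "using mixed effects linear regression to account for clustering within schools". One covariate is fixed: "Adjustment for baseline dietary quality and PA levels will be included in the relevant models". The rest depend on the data. The section accepts that disparities between arms may remain despite minimisation, and says of them: "These will be assessed prior to analysis and relevant confounders will be incorporated in the models". It then lists candidates in open form, with deprivation measured by IDACI score: "factors to be considered include gender, exact age at recruitment and household area of deprivation". No minimisation factor appears in that sentence or elsewhere in the section.

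**The concern.** Minimisation makes the treatment estimate less variable than under simple randomisation when its factors predict the outcome. A model without those factors does not register this. Their contribution stays in the between-school residual variance, so the reported standard error exceeds the true sampling variability. Confidence intervals are then too wide and the test rejects a true null less often than its nominal level.

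The covariate rule makes this likely here. It admits covariates after a check for baseline disparity, and the minimisation factors are the variables the design has made least likely to show one.

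The protocol also gives a reason to expect at least one factor to matter. The section on professional development for teachers states: "Children from more disadvantaged backgrounds are more likely to be overweight/obese, have poorer diets and be less physically active". Free-school-meal share is a school-level marker of disadvantage.

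**Working it through.** **Inputs from the Sample size section.** "Forty-six schools each sending two classes amounting to approximately 50 students from each school and 2300 students in total"; the section also "indicates an intra-school (class) correlation coefficient of 0.035". The target effect is 0.25 SD with 90% power. The significance level is printed as 0.025%. I read it as 2.5% two-sided, because the literal value gives only 49% power.

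**The plan's own figure.**
- Design effect = 1 + 49 × 0.035 = 2.715.
- Effective n per arm = 1150 / 2.715 = 423.6.
- SE of the difference = √(2 × 2.715 / 1150) = 0.0687 SD.
- Power = 91.9% by normal approximation and 90.2% by t with 46 − 2 = 44 df.

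The stated 90% is reproduced, and it uses no covariates.

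**Would the rule select the factors?** The protocol does not define a disparity. Taking p < 0.05 as an assumed definition, with 46 schools, three binary factors and minimisation that follows the balancing arm with probability 0.8 (also assumed), a minimisation factor was selected about once in 54,000 factor checks in simulation.

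**Limiting case: no help from baseline adjustment.** The variance of a school mean is 0.035 + 0.965/50 = 0.0543, and the SE is √(4/46 × 0.0543) = 0.0687. If the factors explain a share R² of between-school variance (assumed; the protocol gives no figure), including them gives SE = √(4/46 × [0.035(1 − R²) + 0.0193]). At R² = 0.50 this is √(4/46 × 0.0368) = 0.0566. Simulation (46 schools, 4000 runs per setting) gave:

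| R² | Mean SE, omitted / included | Type I error, omitted | Power at 0.25 SD, omitted / included |
|---|---|---|---|
| 0 | 0.0682 / 0.0686 | 2.5% | 89.9% / 89.4% |
| 0.25 | 0.0685 / 0.0629 | 1.4% | 91.3% / 94.3% |
| 0.50 | 0.0688 / 0.0567 | 0.9% | 93.4% / 98.1% |
| 0.75 | 0.0686 / 0.0493 | 0.6% | 94.5% / 99.5% |

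At R² = 0.50 the true sampling SD without the factors was 0.0582, against a reported SE of 0.0688. These rows are the extreme, because the planned model does adjust for baseline.

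**With the planned baseline adjustment.** Assume a pupil-level baseline to follow-up correlation of 0.5, a school-level residual correlation of 0.7, and factors that act equally at both times. With an adjustment slope of about 0.5 and R² = 0.40:
- factor part: 0.40 × 0.035 × (1 − 0.5)² = 0.0035;
- remaining school part: 0.60 × 0.035 × (1 + 0.25 − 2 × 0.5 × 0.7) = 0.01155;
- pupil part: 0.0193 × (1 − 0.25) = 0.014475.

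Omitting the factors: SE = √(4/46 × 0.029525) = 0.0507. Including them: SE = √(4/46 × 0.026025) = 0.0476. Simulation (3000 runs per cell) agrees:

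| R² | SE, omitted / included | Ratio | Power at 0.25 SD, omitted / included |
|---|---|---|---|
| 0.20 | 0.0522 / 0.0509 | 1.03 | 99.0% / 99.2% |
| 0.40 | 0.0505 / 0.0476 | 1.06 | 99.7% / 99.7% |
| 0.60 | 0.0489 / 0.0440 | 1.11 | 99.9% / 99.9% |

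With correlations of 0.6 and 0.8, power is at least 99.8% in every cell. Type I error without the factors is about 1.6% to 2.1% across these settings. The Monte Carlo error is √(0.018 × 0.982 / 3000) ≈ 0.24 points, so the range is a guide. With both correlations at 0.5 and R² = 0.50, the omitted-model SE is 0.0524 against a true SD of 0.0496, and type I error is 1.8%.

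**If the true effect is smaller.** At an assumed 0.15 SD, power is 70% without the factors and 76% with them under baseline adjustment, and 44% against 63% without baseline adjustment.

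**Cost of including them if they do nothing.** Residual df fall from 44 to 41, and power from 90.2% to 90.0%.

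**The case against.** The strongest reply is that nothing has been excluded. The candidate list is introduced as open-ended, the test for entry is relevance as a confounder and not a stated imbalance threshold, and this is a condensed article whose analysis plan is not shown. A reader might infer that the factors have been left out of the model; the document supports only that they are not named. That much of the reply stands. It does not dispose of the point, because the article does state how covariates will be chosen, and that route runs through observed disparities. An analysis plan could put this right only by adding to or departing from the published rule.

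The second reply concerns size. Baseline adjustment is fixed, and stable school characteristics shift baseline and follow-up together, so much of their effect is already removed. IDACI, if used, overlaps with free-school-meal share and would absorb more. This stands: the figures without baseline adjustment should not be read as the expected loss.

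The third reply is that prognostic value is documented only for disadvantage. The protocol links activity and obesity to individual attainment, but does not show that a school's GCSE share predicts Year 8 diet or activity. It also says that the participating students will not have visited LifeLab before. This stands too, and makes the consequence conditional.

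**Conclusion.** The point holds in a limited, conditional form. The primary models do not name the variables used to allocate schools, and the stated way of choosing covariates would tend to miss them. If the factors explain between-school variance left after baseline adjustment, the standard errors overstate the uncertainty by roughly 3% to 11% and the 2.5% tests run at about 1.6% to 2.1%. This rests on assumed explained shares of 20% to 60% and assumed baseline correlations of 0.5 to 0.8. With a weak baseline correlation the conservatism is greater, approaching 0.6% to 1.4% in the limiting case for shares of 25% to 75%. If the factors explain nothing, omission costs nothing.

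Two stronger readings are not supported. A reader might infer that the planned power is compromised. It is not: the 90% was computed without covariates, and simulated power without the factors stays at about 90% or above in every setting at 0.25 SD. A reader might also infer that the primary tests are biased or prone to false positives. The error runs the other way, and the loss is only relative to the model that includes the factors.

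**What to change.** State in the protocol and analysis plan that both primary models include free-school-meal share, GCSE attainment and prior LifeLab participation as prespecified school-level fixed effects, whatever the observed balance, alongside the baseline value of the outcome. Replace the selection of covariates after inspecting baseline disparities with a fixed list, saying in advance whether gender, exact age and IDACI are on it.

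The change takes a sentence or two and no new data, since minimisation already requires the three values for every school. It uses three school-level degrees of freedom out of 44, which costs under 1 point of power if the factors turn out not to be prognostic.
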